### Intervention

#### Standard care

In all wards during baseline assessment and in control wards during the intervention phase, patients will receive standard pharmaceutical care from a pharmacy team in the traditional role of taking the responsibility for the appropriate, safe and cost-effective use of medication from a central pharmacy. This does not include patient contact or direct access to patients' medical records, nor does it include face-to-face contact with the ward doctors or nurses. The activities regarding individual patient pharmaceutical care consists of provision of community pharmacy data to the ward at admission, daily screening of alerts generated by the CPOE-system by the pharmacists during hospitalisation and provision of a discharge medication list for the community pharmacy.

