### Sample size and data analysis

The power calculation is based on the parallel comparison of the number of pADEs per 100 admissions between patients admitted at the intervention ward (with ward-based pharmacy care) and those admitted at the control ward (with standard care). We expect a mean base rate of five preventable ADEs per 100 admissions in the control group. This rate is conservatively estimated, based on the incidence of pADEs per 100 admissions in prospective observational studies in hospitalised patients (pooled mean 2.1%, range: 0.6%-16.2% [4,6-14]) and observed rates in control groups of intervention studies on the effect of clinical pharmacy on pADEs (pooled mean 11.6%, range: 11.4%-12% [16,17,26,35]). The difference in incidence rate between the observational and intervention studies can be predominantly explained by a higher sensitivity of ADE detection methods employed in the intervention studies.

In this study population, we hypothesize a relative reduction in pADEs of 60%. This hypothesis is based on the findings of two controlled studies assessing ward-based pharmacy in non-surgical wards, showing a reduction of 66% and a reduction of 78% [16,17].

With all admissions equally distributed over intervention and control wards, a sample of 964 admissions achieves 80% power at a 0.05 one-sided significance level to detect a reduction in the number of pADEs per 100 admissions from 5 to 2 or below (rate ratio <0.4), resulting from ward-based pharmacy care compared to standard care. To control for ward-specific ADEs at baseline, 480 patients equally distributed over the participating surgical wards, will be included at start. Hence, the total number of patients amounts to 1444 (480 + 964). This number of patients will be distributed over the participating centres according to their proportion of number of admitted patients in the wards.

With the total number of 1444 patients a Poisson regression of the number of pADEs with the type of treatment (intervention or control) as the main covariate of interest can be performed to detect a rate ratio below 0.4 with 80% power at a significance level of 0.05. This is performed while adjusting for other covariates like, for instance, hospital site, ward type, observation period, ADE levels at baseline, and patient age, even if these other covariates explain as much as 50% of the variance in pADE counts by type of treatment.

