## Discussion

Measuring cost-effectiveness of clinical pharmacy is complex. Criteria for such research are not standardized. Recently, several recommendations have been stated in a systematic review [21], such as comparative design including a control group, providing details of clinical pharmacy interventions, considering health benefits, considering the effect of program factors (e.g. type of ward and hospital, and level of expertise of clinical pharmacist), considering applicability in other settings, taking a societal perspective when evaluating clinical pharmacy interventions, and including sensitivity and incremental cost-effectiveness analyses. The present study design meets these criteria.

For this study we choose a parallel design with preceding baseline assessment and with randomisation at ward level to assess the incidence of pADEs at baseline in the participating study wards and to determine the impact of the ward-based pharmacy care as well as to take into account the impact of differences between the observed study wards. Furthermore, a large number of factors are suggested to increase the risk of ADEs in hospitalised patients, such as drug characteristics (e.g. route of administration), patient-specific factors (e.g. number of medications taken) [9] and organisational factors (e.g. communication) [38]. These drug characteristics, patient-specific and organisational factors influence the incidence and severity of ADEs, but it is unknown to what extent. Therefore, the ideal situation to test the impact of a pharmacy team on clinical and economic outcomes would consist of an equal distribution of all these factors in experimental and control group. Straightforward comparison of two wards, with one ward only experimental and the other ward only control patients, implies the risk of unbalanced confounders because of the differences between the wards, patients and its staffing. By adding a baseline assessment it is possible to adjust for a priori differences between wards. In this manner a clear insight of the sole impact of the ward-based pharmacy care on pADEs is obtained.

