We choose not to randomise at patient level within a ward because this would imply that one medical team provides care to both experimental and control patients concurrently. The drawback of this design is that the medical staff confronted with the pharmacy team has an increased awareness level of medication safety while they are treating control patients at the same time. This effect is know as the 'Hawthorne effect'--affecting the standard care in control patients [39]. In other words, experimental and control patients in one ward together implies a substantial risk of contamination of arms and thus blurring of effects on outcomes. Therefore, we choose a randomised design on ward level. Thus, in each participating centre, one ward is assigned as experimental (intervention) ward, whereas the other(s) will serve as control ward.

To reduce the risk of confounding, a spaced randomised design including 'cross over' would be desirable. Hereby each ward will serve as control and experimental ward separated with a wash-out period. However, this design was considered of limited value, because wash-out of learning experiences in the intervention arm at a ward during latter sequence might not be successful and the control period might thus become biased. Furthermore, this design is time consuming and may not be needed if extensive baseline assessments are done. Moreover, because of the long wash-out period needed, uncontrolled and unknown changes in factors associated with the risk of ADEs may have occurred.

The participation of three different types of hospitals, an university teaching hospital, a large teaching hospital and a community hospital, strenghtens the general applicability and effectiveness of ward-based pharmacy to various clinical settings.

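### The 80% power claimed for the adjusted Poisson regression on 1444 patients is not supported at 5 pADEs per 100: it is about 50% to 78% one-sided, depending on which covariates are adjusted for

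*Protocol article*

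**What the plan says.** All figures are in the Protocol article, section Sample size and data analysis. The planning rate is stated as: "We expect a mean base rate of five preventable ADEs per 100 admissions in the control group". The target is a fall to 2 per 100, a rate ratio of 0.4. For the parallel comparison, "With all admissions equally distributed over intervention and control wards", the article says that "a sample of 964 admissions achieves 80% power at a 0.05 one-sided significance level". It then adds 480 baseline patients, spread equally over the wards, for a total of 1444.

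A separate sentence claims 80% power at 0.05 for a Poisson regression on all 1444. The adjustment covariates are given as examples: site, ward type, observation period, baseline ADE levels and age. The power is said to hold "even if these other covariates explain as much as 50% of the variance in pADE counts by type of treatment". The section ends by planning to recalculate the sample size once baseline pADE counts are known.

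The section Standard care fixes what the baseline patients receive: "In all wards during baseline assessment and in control wards during the intervention phase, patients will receive standard pharmaceutical care". The Discussion gives the purpose of the baseline: "By adding a baseline assessment it is possible to adjust for a priori differences between wards". It also says, among other arguments against a crossover, that such a design "may not be needed if extensive baseline assessments are done".

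**The concern.** The 480 baseline patients are counted towards a power claim for the treatment effect, yet none of them is treated. They can inform the ward and period terms, but they do not bring the treated share of the 1444 to one half.

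The 50% allowance is also described as variance in pADE counts. In the Poisson-regression sample size formula that yields 1444, the R-squared is the share of variance of the treatment indicator that the other covariates explain. Here treatment is by construction the product of intervention ward and intervention phase, so two of the things to be adjusted for largely determine it.

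What is at stake is the analysis that the Discussion relies on to separate the intervention from prior ward differences. Readers are told that this analysis has a 20% chance of missing the planned effect. If the chance is materially higher, a non-significant adjusted result carries less information than the article implies.

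**Working it through.** **Inputs (Protocol article).** Control rate 0.05 and rate ratio (RR) 0.4, so ln RR = −0.916 and its square is 0.840. One-sided alpha 0.05 (z = 1.645); power 80% (z = 0.842). Study phase 482 and 482. Baseline 480, taken as 240 and 240 (assumption: equal numbers of intervention and control wards). Admissions independent.

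**1. The 964.** Difference of two Poisson rates: n per arm = (1.645 + 0.842)² × (0.05 + 0.02) / 0.03², a total of 962. This reproduces.

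**2. The 1444.** With p the treated share:

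N = [1.645·√(1/(p(1−p))) + 0.842·√(1/(1−p) + 1/(p·RR))]² / [0.05·(ln RR)²·(1−R²)]

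With p = 0.5 and R² = 0.5: (1.645 × 2 + 0.842 × 2.646)² / (0.05 × 0.840 × 0.5) = 30.43 / 0.0210 = 1450, and power at 1444 is 79.9%. The two-sided version gives 1800, so the claim is one-sided with half of the patients treated.

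**3. The design's treated share.** p = 482/1444 = 0.334. With R² still 0.5, N for 80% is 1722 and power at 1444 is 74.9%.

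**4. R² of the treatment indicator.** With cells of 240, 240, 482 and 482, ward group (intervention or control ward) explains 50.1% of the variance of the treatment indicator and period explains 24.9%. Ward group and period are balanced against each other, so together they explain 75.1%. With R² = 0.75 and p = 0.334 the formula gives 55.4%.

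**5. Direct calculation.** Expected events are 240 × 0.05 = 12 in each ward group at baseline, 482 × 0.05 = 24.1 in study-phase controls, and 482 × 0.02 = 9.64 in the intervention cell. Power = Φ(0.916/SE − 1.645) one-sided, with 1.96 in place of 1.645 two-sided.

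| Adjusted for | Var(log RR) | SE | One-sided | Two-sided |
|---|---|---|---|---|
| neither | 1/48.1 + 1/9.64 = 0.125 | 0.353 | 82.9% | 73.8% |
| period only | 1/24.1 + 1/9.64 = 0.145 | 0.381 | 77.6% | 67.2% |
| ward group only | 1/12 + 1/9.64 = 0.187 | 0.433 | 68.2% | 56.3% |
| ward group and period | 1/12 + 1/12 + 1/24.1 + 1/9.64 = 0.312 | 0.558 | 49.8% | 37.5% |

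A simulation of 40,000 trials with a likelihood-ratio test gave 50.4% and 38.4% for the last row. The period-only row is the parallel comparison of 964 on the log scale: the baseline patients drop out of its variance. Its gap to 80% is therefore small and partly a matter of test scale.

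**6. What would give 80% in the last row (one-sided).**
- A rate ratio near 0.20: the variance becomes 0.1667 + 0.0415 + 1/4.82 = 0.416, SE 0.645, z = 1.609/0.645 = 2.50, power about 80%.
- A control rate near 11.6 per 100: SE 0.367, power 80.3%. At 10 per 100 it is 75.0%.
- At 5 per 100 and RR 0.4, about 1444 × (2.487 × 0.558/0.916)² ≈ 3,320 patients in the same proportions.

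**The case against.** **The model is not specified.** The covariates are examples, and ward type is not ward identity. A reader might infer that the planned analysis simply has 50% power. The article does not support that. The 50% needs both ward group and period in the model; lighter adjustment gives 68% or 78%. What remains is that each of these adjusted readings is below 80% at 5 per 100, and that correcting only the treated share gives 75% at the article's own R-squared.

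**A recalculation is planned.** The article considers its control rate probably conservative and will revisit the sample size after baseline. At its pooled rate of 11.6 per 100 from intervention studies, even the ward-and-period contrast has 80% one-sided. This bears on how serious the shortfall will prove. It does not make the sentence true at 5 per 100, and a recalculation that repeated the half-treated split would repeat the error.

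**The primary basis is the parallel comparison.** This is correct, and the 964 stands as calculated. A reader might infer that the whole sample size is wrong, but the error lies in the added claim about 1444.

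**The role of the baseline.** A reader might infer that the baseline assessment is the reason for rejecting a crossover, or that a null result will be read as no benefit. The Discussion also cites incomplete wash-out of learning, time, and uncontrolled changes during a long wash-out. The article does not say how a null result will be interpreted.

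**Conclusion.** The claim of 80% power for the adjusted regression on 1444 patients is wrong as written at 5 pADEs per 100. It rests on a half-treated sample that the design does not have, and on a 50% allowance that ward group and period alone exceed. One-sided power is about 50% with both in the model and up to 78% with less adjustment; with both, it is 37% two-sided. The low figure matters most, because only that contrast uses the baseline to remove prior ward differences while allowing for period.

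These figures assume independent admissions and a 1:1 ward split. Clustering within wards would lower them. More control than intervention wards lowers the 50% slightly: 49.5% at 4:3 and 47.8% at 6:3.

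**What to change.** In Sample size and data analysis:

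- Keep the list of covariates and delete only the clause "even if these other covariates explain as much as 50% of the variance in pADE counts by type of treatment".
- State that 80% power (one-sided 0.05, independent admissions) applies to the unadjusted parallel comparison of 964, and remove the 80% from the sentence on 1444.
- In its place, give the adjusted power for a rate ratio of 0.4 at 5 per 100: about 50% one-sided with ward and period both in the model, and up to 78% with less adjustment.
- Base the planned recalculation on the actual one-third treated share and on the ward-by-period contrast, using the observed baseline rate.
- Say that a non-significant adjusted result will be interpreted through its confidence interval.

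The cost is a less favourable stated power. The restatement itself requires no extra patients; whether more are needed is for the recalculation to show.

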#### Economic evaluation

The economic evaluation of ward-based pharmacy care compared with standard care will be performed as a cost-effectiveness analysis from a societal perspective with the costs per preventable ADE as the primary outcome measure. Although fewer ADEs may result in reduced utilization of hospital resources, the savings may well be offset by increased pharmacy staff time. The time horizon of the evaluation will be three months following the initial admission to the surgery ward. This follow-up period will most probably include the full hospital admission as well as some time post-discharge. With this short time-span, costs and effects will not be discounted. Incremental cost-effectiveness ratios will be calculated, reflecting the difference in costs between ward-based pharmacy care and standard care relative to the difference in number of preventable ADEs.

Sensitivity analyses will be performed to account for sampling variability, plausible ranges of ward costs of various health care components, the substitution of pharmacists by pharmacy technicians and the weighing of preventable ADEs by level of severity based on expert opinion and using the CTCAE classification system. Furthermore, scenario analyses will be performed to account for differential allocations of ward-based pharmacy care during admissions. By monitoring the occurrence of preventable ADEs during admissions, ADE risk profiles over time (e.g. probabilities of events at day 1, day 2, etc.) can be constructed and used to develop scenarios for discontinuous or intermittent ward-based pharmacy care during admissions. Such scenarios may save costs which can be weighed against the risk of missing preventable ADEs.

Unit costs resources used will be derived from the most actual Dutch costing guideline for health care research [36]. The friction costs method will be applied to derive the costs of productivity loss due to sick leave from work [37]. After price-indexing all costs will be expressed in Euros for the base year 2010.

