**Methods/Design:**

A multi-centre controlled trial, with randomisation at ward-level and preceding baseline assessments is designed. Patients admitted to the surgical study wards for elective surgery with an expected length of stay of more than 48 hours will be included. Patients admitted to the intervention ward, will receive ward-based pharmacy care from the clinical pharmacy team, i.e. pharmacy practitioners and hospital pharmacists. This ward-based pharmacy intervention includes medication reconciliation in consultation with the patient at admission, daily medication review with face-to-face contact with the ward doctor, and patient counselling at discharge. Patients admitted in the control ward, will receive standard pharmaceutical care.

The primary clinical outcome measure is the number of pADEs per 100 elective admissions. These pADEs will be measured by systematic patient record evaluation using a trigger tool. Patient records positive for a trigger will be evaluated on causality, severity and preventability by an independent expert panel. In addition, an economic evaluation will be performed from a societal perspective with the costs per preventable ADE as the primary economic outcome. Other outcomes of this study are: severity of pADEs, number of patients with pADEs per total number of admissions, direct (non-)medical costs and indirect non-medical costs, extra costs per prevented ADE, number and type of pharmacy interventions, length of hospital stay, complications registered in a national complication registration system for surgery, number of readmissions within three months after initial admission (follow-up), quality of life and number of non-institutionalized days during follow-up.

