### Study outcomes and data collection

The primary outcome parameter is the number of preventable ADEs per 100 admissions. Secondary outcome parameters are severity of preventable ADEs, number of patients with preventable ADEs per total number of admissions, direct (non-)medical costs and indirect non-medical costs, extra costs per prevented ADE, number and type of pharmacy interventions, length of hospital stay, complications registered in a national complication registration system for surgery, number of readmissions within three months after the initial admission (follow-up), quality of life during follow-up and number of non-institutionalized days during follow-up.

To assess the incidence and severity of preventable ADEs, we will systematically evaluate patient records and the hospital information system by use of a developed and validated Trigger Tool. This tool is based on previously literature on trigger tools, such as the trigger tool for measuring harm in ICU patients [22], the trigger tool for detection of AEs in surgical patients [23] and the widely used Global Trigger Tool of the Institute for Healthcare Improvement [24,25]. This list of items, or triggers, are clues to identify potential pADEs. Previous studies have shown that a trigger tool can efficiently and consistently be applied to detect and identify preventable ADEs [26,27]. If patient records are positive for potential pADE triggers, an independent expert panel, consisting of senior hospital pharmacists and consultant surgeons, will assess the presence or absence of the potential pADE individually, blinded for the hospital and ward the patient was admitted to. They will determine the presence or absence by use of a causality assessment tool for surgical patients based on tools such as the Naranjo probability score and the WHO-UMC [28,29].

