Besides causality assessment, the expert panel will also determine the severity of the ADE by use of a classification system called Common Terminology Criteria for Adverse Events (CTCAE) developed by the U.S. National Cancer institute [30]. This list is preferred, because a grading scale is provided for each AE term, in contrast to the National Coordinating Council for Medication Error Reporting and Prevention index (NCC MERP) [31]. Furthermore, the expert panel will assess the additional impact of each pADE to a patient's life, given his disease status. Discrepancies between the individual assessments will be discussed at consensus meetings of the experts.

For the economic evaluation, we will collect direct medical costs of all included admissions, such as diagnostic examinations, therapeutic interventions as well as the costs of monitoring by hospital pharmacists during hospitalization. Most data will be extracted from the hospital information system. Specifically, registration of tasks performed by the clinical pharmacy team will be done, not just as input values for the cost estimates, but also to support implementation decisions in anticipation of the program's cost-effectiveness. Moreover, we will gather information on direct (non-)medical costs, such as costs of out-patients care, out-of-hospital care and, if opportune, readmissions, as well as on indirect non-medical costs, such as productivity losses, by sending a patient questionnaire at three months following hospital admission. This questionnaire consists of an adapted version of the Health and Labour questionnaire developed by the Institute for Medical Technology Assessment in the Netherlands [32].

Besides cost-related questions, the validated EQ-5D questionnaire is used at three months after the initial admission to measure the quality of life of the patient [33]. The EQ-5D instrument contains five dimensions (mobility, self care, usual activities, pain/discomfort and anxiety/depression) for which patients have to indicate whether they experienced no, some or severe/extreme problems. In addition, patients have to assess their health status on a Visual Analogue Scale (VAS), ranging from zero for the worst imaginable health state to 100 for the best imaginable health state [33].

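### The primary economic outcome is labelled inconsistently, and the incremental cost-effectiveness ratio is defined without stating the baseline adjustment that the plan relies on for pADEs

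*Protocol article*

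**What the plan says.** The Abstract (Methods/Design) describes an economic evaluation from a societal perspective "with the costs per preventable ADE as the primary economic outcome". The Economic evaluation section repeats this: "with the costs per preventable ADE as the primary outcome measure". The Abstract's list of other outcomes and the secondary list in Study outcomes and data collection carry a differently worded item, "extra costs per prevented ADE". The Economic evaluation section then announces incremental cost-effectiveness ratios, "reflecting the difference in costs between ward-based pharmacy care and standard care relative to the difference in number of preventable ADEs". It does not say that this ratio is the primary outcome, and it names no adjustment for either difference. Its sensitivity analyses cover sampling variation, ranges for ward costs, replacement of pharmacists by technicians, and severity weights. Pre-existing differences between wards are not among them.

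For the clinical outcome, Sample size and data analysis plans a Poisson regression of pADE counts that adjusts for covariates such as site, type of ward, study period, baseline ADE level and age. The Discussion gives the reason: "Straightforward comparison of two wards, with one ward only experimental and the other ward only control patients, implies the risk of unbalanced confounders". It describes the ideal of balanced factors for clinical and economic outcomes together and offers the baseline assessment as the remedy, but claims the resulting clear reading for pADEs only. On cost data, Study outcomes and data collection says: "we will collect direct medical costs of all included admissions".

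**The concern.** Two things are left unsettled for the trial's second main question, cost-effectiveness.

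First, the Abstract carries the cost-per-pADE label and the extra-cost-per-prevented-ADE label side by side as different outcomes, so they cannot simply be read as synonyms. Taken at its word, the primary one is an average: total cost divided by the number of events. Its denominator shrinks when the intervention prevents events, so success makes it look worse.

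Second, the plan's protection against ward differences is written for pADE counts only. Each of three centres has one intervention ward, allocated once. Randomising so few wards cannot be relied on to balance case-mix or cost. If the ICER were built from crude differences, its numerator could carry a ward cost difference that predates the intervention, and its denominator could differ from the effect reported for the first main question.

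**Working it through.** **Inputs from Sample size and data analysis.** Control rate 0.05 pADEs per admission, intervention rate 0.02 (rate ratio 0.4), 964 admissions in equal arms, 80% power, one-sided 0.05; 1444 in total, with other covariates explaining up to 50% of variance. The article gives no cost figure, so every euro amount below is an assumption.

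**Reproducing the plan's figures, to confirm the rates.**
- Difference of two Poisson rates: n per arm = (1.645 + 0.842)² × (0.05 + 0.02) / 0.03² ≈ 481, total 962, against 964 stated.
- Poisson regression with a binary covariate at 50%: N = (1.645 × √4 + 0.842 × √(1/0.5 + 1/(0.5 × 0.4)))² / (0.05 × (ln 0.4)²) ≈ 725. Dividing by (1 − 0.5) gives 1450, against 1444 stated.

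Both agree within 0.5%, so 5 and 2 per 100 are the rates to use.

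**The label read literally.** With equal cost C per admission:
- control: C / 0.05 = 20C
- intervention: C / 0.02 = 50C, which is 2.5 times higher (1/0.4).

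To hold the ratio level, the intervention cost must satisfy C₁ / 0.02 = C / 0.05, so C₁ = 0.4C, a 60% fall in mean cost. With an assumed EUR 10,000 under control and EUR 9,000 under intervention, the literal ratio still rises from 200,000 to 450,000. The incremental ratio is (9,000 − 10,000) / 0.03 = −33,333: cheaper and more effective. The two labels then give opposite messages on the same data.

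**Sensitivity of an unadjusted numerator.** Each EUR 100 of prior ward cost difference per admission moves the ratio by 100 / 0.03 = EUR 3,333. With an assumed true extra cost of EUR 200, the adjusted ratio is 200 / 0.03 = 6,667 and the unadjusted one is (200 + d) / 0.03:

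| Prior ward cost difference d (EUR) | Unadjusted ICER (EUR per pADE prevented) |
|---|---|
| −300 | −3,333 |
| −100 | 3,333 |
| 0 | 6,667 |
| +100 | 10,000 |
| +300 | 16,667 |

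**Sensitivity of an unadjusted denominator.** Let the intervention wards' baseline pADE rate be b times that of the control wards, with true rate ratio 0.4. The crude difference is 0.05 − 0.05 × b × 0.4. For b = 0.5 it is 0.04 and for b = 1.5 it is 0.02. At an extra cost of EUR 200 the ratio runs from 5,000 to 10,000, against 6,667 when standardised to the control rate.

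**The case against.** The strongest reply is that the ICER sentence is a generic definition. It fits adjusted differences as well as crude ones, and an article may leave the modelling of costs to the full plan. That stands. A reader might infer that the ICER will be crude, or that baseline costs will be discarded; the article says neither.

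A reader might also infer that the plan calls its own economic contrast confounded. It does not. The Discussion speaks of a risk attached to a straightforward comparison of two wards, and does so to explain why the baseline assessment was added. Wards are randomised within centres, so a prior cost difference would be chance imbalance among few wards. The article does not say that intervention and control wards differ in case-mix.

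On the label, the section that names cost per pADE goes on to define the incremental ratio, the Background promises incremental analyses, and nowhere is an average cost per pADE in each arm proposed. The intent is therefore probably right. What remains is that the article names one quantity as primary, lists a differently worded one as secondary, and does not say which of them the ICER is.

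On adjustment, what remains is narrower: the Discussion raises balance for economic outcomes, yet adjustment is written down only for pADEs.

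**Conclusion.** The point holds as an inconsistency of labelling and an unstated extension of the adjustment, not as a demonstrated flaw in the analysis. The labelling part is firm: it rests on the article's wording and its own rates, and the 2.5-fold rise follows at any equal cost. The adjustment part is supported in substance, because the plan's own reason for adjusting covers economic outcomes while its stated adjustment does not.

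The EUR 3,333 per EUR 100 follows from the planned difference of 3 per 100; the size of any prior cost difference and the EUR 200 extra cost are assumptions. The table shows that an unadjusted ratio could change sign at a large enough imbalance. A reader might infer that the cost-effectiveness conclusion would reverse, but without cost data or a decision threshold the document cannot support that. The correction is cheap and worth making before the economic data are analysed.

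**What to change.** - Name incremental cost per pADE prevented as the single primary economic outcome in the Abstract, in Study outcomes and data collection, and in Economic evaluation. Drop the duplicate secondary entry.
- Take the ICER denominator from the same baseline-adjusted contrast as the primary pADE analysis. Because the Poisson model yields a rate ratio, state the reference rate at which it is turned into a difference.
- Estimate incremental hospital cost with the same ward and period adjustment, using baseline-phase hospital costs. The commitment to collect costs for all included admissions, read together with the 480 patients included at the start, indicates that these will be available.
- Adjust out-of-hospital and productivity costs in this way only if baseline patients also receive the three-month questionnaire, which the article text does not say. If they do not, state how the societal total will combine adjusted and unadjusted components.
- Let the uncertainty reflect the joint distribution of costs and pADEs and the allocation by ward. Resampling patients only within ward and phase would omit between-ward variation.

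The cost is a wording change, some extra analysis and a wider interval. No new hospital cost data are needed if baseline collection proceeds as the text indicates.
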